### Implementation

The second author will generate the allocation sequence. All authors will participate in enrolling and assigning participants. The names of the treatment groups were placed into envelopes per the randomization sequence, sealed, and labeled with a sequential participant number. Once a patient consented to participate, a researcher who is on call that time will open the envelope to reveal the name of the assigned group.

## Assignment of interventions: blinding

Both of the modes have parameter adjustment on the ventilator; respiratory therapists and attending physicians will not be blinded due to the nature of the study. Blinding was set for the remaining study personnel like statistician, patients, and families. There will be no circumstances under which unblinding is permissible, as the respiratory therapists will not be blinded due to the nature of the study and family members are not allowed to get into the NICU due to the hospital policy. To minimize bias, “ventilator adjusting protocol” and “criteria for extubation” have been carefully defined and adhered.

### Primary outcome

Death or BPD at 36 weeks’ postmenstrual age will be used as the primary outcome. BPD will be diagnosed by clinical physicians. The definition and diagnostic criteria of BPD is according to NIH 2018 [16]. We have chosen “death or BPD (36w)” as our primary outcome to maintain similarity with previous trial comparing VTV and PCV [10].

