### Strategies to improve adherence to interventions

To improve adherence to research interventions, a flow sheet will be displayed at each bedside as a reminder to the respiratory therapists or physicians of the allowed parameter adjustment.

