## Data collection and management

### Data collection

Data will be collected on a web-based electronic case record form by research investigators. Some collected data can be obtained from the clinical records, and the rest will be collected from the ventilator at the bedside. Clinical information will be collected in three forms at the following times: demographic information will be collected at trial entry, baseline information will be collected after randomization, and outcome information: including primary outcomes, secondary outcomes, and others. Outcomes will be collected before discharge. And other observational information like ABG, ventilator settings, and respiratory mechanics will be collected 1 h after using the ventilator and same time each day until extubation.

Any participants who discontinue or deviated from the intervention protocol has to collect the specific reason.

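### BPD, the only non-fatal part of the primary outcome, is diagnosed by clinical physicians none of whom is described as blinded; a rule applied by the blinded statistician would remove bias at the labelling step

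*Protocol article*

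**What the plan says.** All references are to the protocol article.

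- **Primary outcome:** "Death or BPD at 36 weeks’ postmenstrual age will be used as the primary outcome". The next sentence assigns the diagnosis: "BPD will be diagnosed by clinical physicians". The one after gives the criteria: "The definition and diagnostic criteria of BPD is according to NIH 2018 [16".
- **Assignment of interventions: blinding:** "respiratory therapists and attending physicians will not be blinded due to the nature of the study". Then: "Blinding was set for the remaining study personnel like statistician, patients, and families". No outcome assessor is named among those blinded. On bias control the section says: "To minimize bias, “ventilator adjusting protocol” and “criteria for extubation” have been carefully defined and adhered".
- **Strategies to improve adherence to interventions:** "a flow sheet will be displayed at each bedside as a reminder to the respiratory therapists or physicians", showing the adjustments that are allowed.
- **Data collection:** outcome information has its own form, completed before discharge, and clinical records are an allowed source.
- **Secondary outcome:** durations of invasive ventilation, noninvasive ventilation and oxygen use are collected.

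**The concern.** Death needs no judgement about the label. BPD does, even under a published definition: someone has to decide which support counts at the reference date and whether the criteria are met. The article gives that step to clinical physicians and does not say that they are kept unaware of the arm. Attending physicians and respiratory therapists are expressly unblinded, and a sheet of allowed adjustments hangs at the bedside.

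The trial is designed to show superiority of VTV, and the Discussion hopes for evidence of its benefits. If borderline infants are labelled a little more leniently in one arm than in the other, the error enters the primary comparison directly. Intention-to-treat analysis does not correct it, because that protects the allocation and not the measurement of the outcome.

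**Working it through.** **1. The sections side by side.**

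| Question | What the article states | Where |
|---|---|---|
| Who labels BPD? | Clinical physicians | Primary outcome |
| By what criteria? | A published definition | Primary outcome |
| Who is unblinded? | Respiratory therapists, attending physicians | Blinding |
| Who is blinded? | Remaining personnel; statistician, patients and families as examples | Blinding |
| Which bias safeguards are named? | Ventilator adjusting protocol, extubation criteria | Blinding |

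Nothing in the table covers knowledge of the arm when the label is assigned.

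**2. Size of a possible error.** The plan gives no figure on this point, so there is none to reproduce. Every rate here is an assumption.

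- T = true death/BPD rate, the same in both arms: 0.45
- D = part of T that is deaths: 0.15, so BPD without death is 0.30
- m = share mislabelled: BPD cases missed under VTV, non-cases labelled BPD under PCV

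Recorded VTV rate = D + (1 − m)(T − D). Recorded PCV rate = T + m(1 − T).

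- m = 0.10: VTV = 0.15 + 0.90 × 0.30 = 0.420; PCV = 0.45 + 0.10 × 0.55 = 0.505; false difference 0.085.
- m = 0.05: VTV = 0.15 + 0.95 × 0.30 = 0.435; PCV = 0.45 + 0.05 × 0.55 = 0.4775; false difference 0.0425.

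Subtracting the two formulas gives m(T − D) + m(1 − T) = m(1 − D). The false difference therefore depends on the mislabelling rate and the death rate, but not on T:

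| Deaths D | m = 0.05 | m = 0.10 |
|---|---|---|
| 0.05 | 4.75 points | 9.5 points |
| 0.15 | 4.25 points | 8.5 points |
| 0.25 | 3.75 points | 7.5 points |

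**3. Against the design difference.** Sample size assumes 26% against 64%, a gap of 38 points. The false differences at D = 0.15 are 8.5/38 = 22% and 4.25/38 = 11% of that gap.

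**4. Effect on the test.** With 68 infants there are 34 per arm. Summing the binomial probabilities of all outcomes for which the two-sided pooled z-test at 0.05 is significant in favour of VTV, with no true difference, gives:

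- no mislabelling (45% in both arms): 2.4%
- m = 0.05 (43.5% against 47.75%): 5.1%
- m = 0.10 (42.0% against 50.5%): 9.8%

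Mislabelling at these rates would about double or quadruple the chance of a false finding for VTV.

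**The case against.** **The definition is published, so the label is close to objective.** This is the strongest point, and it partly stands. Criteria fixed in advance narrow the room for judgement, and the mislabelling rates above may be too high. But a definition does not settle whether the person applying it knows the arm. If the criteria can be applied almost mechanically, blind application is also easy.

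**The diagnosing physicians may not be the unblinded ones.** A reader might infer that the treating physicians themselves make the diagnosis. The article does not say so: it unblinds attending physicians, has clinical physicians diagnose, and leaves the list of blinded personnel open. What stands is narrower: no diagnosing physician is described as blinded.

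**The data needed for a blind derivation are missing.** A reader might infer this from the collection of observational data at the "same time each day until extubation". The inference fails. That limit applies to blood gases, ventilator settings and respiratory mechanics. Outcome information is collected separately before discharge, durations of noninvasive support and oxygen are recorded, and clinical records may be used. The assessment schedule (Fig. 1) is not shown either, so nothing can be concluded about a 36-week entry.

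**The error could be put at 10 points.** Taking 10% off the whole VTV composite gives 0.45 × 0.90 = 40.5% against 50.5%. That is too large, because it lets deaths go undiagnosed.

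**Blind labelling leaves the larger problem.** Unblinded staff also choose the support on which the label depends, and a blind rule carries those choices into the outcome. This stands and limits the gain.

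**Conclusion.** The concern holds at the labelling step. The article has the only non-fatal component of the primary outcome diagnosed by clinical physicians, describes none of them as blinded, and names safeguards only for ventilator adjustment and extubation. The published definition reduces the risk but does not remove it.

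Under the stated assumptions the false difference is about 4 to 8.5 points at 15% deaths, and 3.75 to 9.5 points over the wider range shown. That is well short of the 38-point design difference, but enough to raise the one-directional false-positive rate from 2.4% to between about 5% and 10%. The mislabelling rates and the death share are illustrative. The documents do not show that such bias will occur, or that the primary result would be invalid. The case for change is that a less exposed method is available at little cost.

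**What to change.** In Primary outcome, replace the sentence on who diagnoses BPD with a statement to this effect:

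- BPD status for the primary analysis is derived by a fixed rule, written before any comparison by arm, from the items that the cited definition requires at 36 weeks' postmenstrual age.
- Those items are transferred from the clinical record to the existing outcome form. The list must be taken from the definition itself.
- The blinded statistician applies the rule to a file without the arm, the charted diagnosis, or ventilator variables that could reveal the mode.
- The clinicians' diagnosis is kept and analysed as a sensitivity analysis.

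**Cost.** A few form entries for each of 68 infants and a short written rule, with no extra reader, procedure or change in sample size. Recruitment has begun, so the change needs the formal amendment described under Protocol amendments, and values for infants already past 36 weeks would be sought in their records.

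**What it does not do.** Bias in the unblinded choice of support level remains and should be acknowledged as a limitation.

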### Secondary outcome

BPDDeathLength of invasive MV, noninvasive mechanical ventilation, and oxygen useLength of hospital stayFailure of conventional MV. Rate of using HFOV as rescue therapyCriteria for the failure of conventional MV (meet any one or more of these points):i.Infants with 100% inhaled oxygen concentration and MAP ≥ 15 cmH_2_O have oxygen saturation (SpO_2_) less than 90% or two blood gasses monitored at least 2 h apart show partial pressure of oxygen (PaO_2_) less than 50 mmHgii.Inability to maintain PCO_2_ < 60 mmHg and pH < 7.25 with conventional MV modeiii.Clinical manifestations confirming unsuitability for use of the current mode, for example, air leak syndrome and severe pulmonary hemorrhage, etc.iv.The clinical team consider the infant’s current clinical condition unsuitable for the continuation of the current mode of ventilationRate of reintubation within 48 hThe risk of complications: air leak syndrome, grades 3 to 4 intraventricular hemorrhage (IVH), periventricular leukomalacia (PVL), stage 3 or higher retinopathy of prematurity (ROP), necrotizing enterocolitis (NEC), pulmonary hemorrhageHospital expenses

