### Sample size

An RCT of VLBW infants with respiratory distress syndrome(RDS) receiving VTV or PCV as their primary respiratory support mode showed that the BPD/death rate of 26% and 64% respectively [15]. Based on this study, a sample size of 31 in each group will have 90% power to detect statistically difference at a 0.05 tow-sided significance level (MedSci, Shanghai, China). Considering a 20% of patients may withdraw from the research, a sample size of 68 will be appropriate.

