### Methods in analysis to handle protocol non‐adherence and any statistical methods to handle missing data

Patients with missing outcome data will be censored at last contact. Descriptive statistics on the use of non-protocolized modes as well as intolerance of conventional ventilation mode (duration in days and percentage of time in study spent on HFOV) will be provided.

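### Criterion ii for failure of conventional ventilation pairs a PCO2 state to be kept with a pH state that can only be a failing one, so this secondary outcome can be misclassified

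*Protocol article*

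**What the plan says.** The Secondary outcome section of the protocol article lists failure of conventional ventilation, in the same item as HFOV rescue, and gives four criteria. Meeting any one is enough.

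- Criterion i is an oxygenation rule with numeric limits. Its PaO2 limb needs two gases at least 2 h apart.
- Criterion ii is the carbon dioxide and pH rule: "Inability to maintain PCO_2_ < 60 mmHg and pH < 7.25 with conventional MV".
- Criterion iii is clinical and open-ended: "for example, air leak syndrome and severe pulmonary hemorrhage, etc".
- Criterion iv is met when the clinical team judges the infant's condition unsuited to continuing the current mode. It has no numeric limit.

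On blinding, the article states that "respiratory therapists and attending physicians will not be blinded due to the nature of the study". The safeguards it names are these: "To minimize bias, “ventilator adjusting protocol” and “criteria for extubation” have been carefully defined and adhered". The declaration of failure is not among them.

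The section on non-adherence and missing data adds that descriptive statistics on "intolerance of conventional ventilation mode (duration in days and percentage of time in study spent on HFOV) will be provided".

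**The concern.** In criterion ii the words about inability to maintain govern both inequalities. For PCO2 this works: the value should stay below the limit, and losing that is failure. For pH the same grammar makes a value below 7.25 the thing to be maintained, which cannot be meant in a list of signs of failure. The sentence therefore has no consistent reading as printed.

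Staff have to repair it for themselves, and there is more than one way to do so. Because one criterion suffices, a gas result classified differently under criterion ii can change the infant's status on the whole outcome. At stake are the count of failures in each arm and their difference.

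This is not a detail that a fuller protocol or an analysis plan would normally supply. The article states a complete criterion, and that criterion contradicts itself. The Definitions section does not help: it describes discontinuation through difficulty with oxygenation and says nothing of carbon dioxide or pH.

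**Working it through.** The article gives no planned or expected rate for this outcome, so there is no figure to reproduce. The check is a truth table. Its inputs are the two limits in criterion ii (PCO2 60 mmHg, pH 7.25) and five gas results chosen here for illustration.

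Three readings are possible:

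- A, literal: failure = NOT (PCO2 < 60 AND pH < 7.25).
- B, pH below the limit taken as a failing state, both required: failure = PCO2 ≥ 60 AND pH < 7.25.
- C, pH below the limit taken as a failing state, either sufficient: failure = PCO2 ≥ 60 OR pH < 7.25.

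| PCO2 (mmHg) / pH | A | B | C |
|---|---|---|---|
| 45 / 7.35 | failure | no | no |
| 50 / 7.30 | failure | no | no |
| 55 / 7.20 | no | no | failure |
| 65 / 7.30 | failure | no | failure |
| 65 / 7.20 | failure | failure | failure |

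All three readings agree only on the last row. Reading A is untenable: it calls the first two infants failures and clears the third. Setting A aside, B and C still disagree on 55/7.20 and 65/7.30, that is, whenever exactly one of the two values is out of range.

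To show how this reaches the between-arm difference, suppose that under reading B the failure outcome is 10% in one arm and 25% in the other, and that a share f of the remaining infants in each arm is counted only under reading C. These rates and f are assumptions; the documents give none of them. Under reading C the rates become 0.10 + 0.90f and 0.25 + 0.75f, and their difference is 0.15 × (1 − f).

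| f | Rates under C | Difference (percentage points) |
|---|---|---|
| 0 | 10% and 25% | 15 |
| 0.1 | 19% and 32.5% | 13.5 |
| 0.3 | 37% and 47.5% | 10.5 |
| 0.5 | 55% and 62.5% | 7.5 |

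If f differs between arms, the difference can move either way. The table shows the mechanism only; it predicts nothing about this trial.

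The data needed to apply a corrected rule are already planned. The section on other collected data lists pH, PCO2, PaO2, SpO2, MAP and FiO2. The Data collection section has gases and settings recorded 1 h after ventilation starts and daily until extubation, and asks for the reason for any discontinuation or deviation. The Definitions section also asks for reasons and ventilator parameters at discontinuation.

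**The case against.** The strongest reply is that nobody at the bedside would apply the literal reading. The surrounding criteria describe hypoxaemia, air leak, haemorrhage and clinical unsuitability, so low pH is evidently meant as a sign of failure. This stands. A reader might infer from the wording that nearly every infant would be counted as failing in both arms, but that follows from the printed logic and is not a forecast. It does not settle whether both values must be out of range or either one.

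Figures 2 and 3, the ventilator protocols, are not in the text available here and may show which direction is intended. That is a fair limit on this point. The printed criterion would still need to be brought into line with them.

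Criterion iv is an understandable provision where the modes cannot be masked. A reader might infer that it turns any switch, or mere preference, into failure. The text does not say so; it asks for a judgment about the infant's condition. Nor would dropping it leave a purely objective outcome, since criterion iii also rests on judgment. What stands is narrower: the judgment is made by unblinded staff and is sufficient alone.

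A reader might also infer that the primary comparison is weakened. The documents do not support that. Death or BPD is analysed by intention to treat and does not use this definition, HFOV use can be counted without criterion ii, and reasons for leaving the assigned mode are to be recorded. Variation between sites does not arise either, because the trial has a single centre. The remaining variation is between members of staff.

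**Conclusion.** The point holds as a defect in one component of one secondary outcome. As worded, criterion ii contradicts itself, and no other section of the article repairs it. Under any sensible reading, infants with only one of the two values out of range can be classified either way, and a single criterion decides the outcome.

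The effect in percentage points cannot be stated, because the documents give neither expected failure rates nor the share of infants with only one value out of range. It would be wrong to conclude that the outcome fails to measure failure at all: criterion i and the events named in criterion iii still capture real failure. The conclusion assumes that the text available here reproduces the criterion correctly and that the missing figures do not restate it in corrected form.

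**What to change.** Amend criterion ii. The sponsor should reconcile its two halves with each other and with the ventilator protocols in Figures 2 and 3, word both in the same direction, and state whether one or both must be present. Which limits are right is for the sponsor to settle.

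Apply the amended wording to all infants, including any already enrolled, using the recorded gases and without reference to outcome by arm. Where the daily gas does not include the one that prompted a change of mode, the documented reason should supply it.

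In addition, code which criterion led to each declared failure and tabulate by arm those declared under criterion iv alone. Criterion iv itself need not change.

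The cost is one sentence in an amendment, which the Protocol amendments section already routes to the ethics committee, and one reason code on a form that already asks for reasons. The small downside is a lower failure count when infants declared under criterion iv alone are shown separately.

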### Other collected data

The following data will be recorded for each infant: demographic information: patient’s record number, gestational age, gender, birthweight, multiple birth, delivery way, antenatal steroid treatment, preterm premature rupture of membranes, chorioamnionitis, maternal eclampsia; baseline information: Apgar score at 1, 5, 10 min, amniotic fluid status, times of using supplementary pulmonary surfactant, small for gestational age, age at intubation (h); other information: ventilator settings and measurements including MAP, fraction of inhaled oxygen concentration (FiO_2_), PIP, Vt, respiratory rate (RR), and minute ventilation. Other vital signs and arterial blood gas (ABG) results including SpO_2_, PaO_2_, pH, PCO_2_, oxygen index, and heart rate.

### Participant timeline

See Fig. 1.

**Fig. 1 Fig1:**
[figure not shown]
Schedules of assessment and procedures

### Intervention

#### Ventilator

Evita V300, Evita V500 (with volume guaranteed module, Draeger, Lubeck, Germany) or Fabian (ACUTRONIC Medical System, Hirzel, Switzerland) will be used depending on which one is available at that time.

Initial ventilator settings and parameter adjustment (Fig. 2).

**Fig. 2 Fig2:**
[figure not shown]
Volume-targeted ventilation protocol for very low birthweight infants

Retest ABG or transcutaneous PCO_2_ 2 h after adjusting parameters (Fig. 3).

**Fig. 3 Fig3:**
[figure not shown]
Pressure-controlled ventilation protocol for very low birthweight infants

Retest ABG or transcutaneous PCO_2_ 2 h after adjusting parameters.

### Extubation criteria

The extubation criteria are as follows: infant’s MAP ≤ 10 cmH_2_O without tachypnea or labored breathing, current weight ≥ 80% of birthweight, and infant has adequate spontaneous breathing.

### Strategies to improve adherence to interventions

To improve adherence to research interventions, a flow sheet will be displayed at each bedside as a reminder to the respiratory therapists or physicians of the allowed parameter adjustment.

### Routine care after extubation

Caffeine could be used to prevent apnea.

Nasal intermittent positive pressure ventilation will be used after extubation.

Re-intubate if clinically indicated.

If the infant was reintubated, the original randomly assigned ventilation mode should be used.

## Data collection and management

### Data collection

Data will be collected on a web-based electronic case record form by research investigators. Some collected data can be obtained from the clinical records, and the rest will be collected from the ventilator at the bedside. Clinical information will be collected in three forms at the following times: demographic information will be collected at trial entry, baseline information will be collected after randomization, and outcome information: including primary outcomes, secondary outcomes, and others. Outcomes will be collected before discharge. And other observational information like ABG, ventilator settings, and respiratory mechanics will be collected 1 h after using the ventilator and same time each day until extubation.

Any participants who discontinue or deviated from the intervention protocol has to collect the specific reason.

